## Abstract

**Background:**

Power-oriented resistance training (PRT) is one of the most effective exercise programs to counteract neuromuscular and physical function age-related declines. However, the optimal load that maximizes these outcomes or the load-specific adaptations induced on muscle power determinants remain to be better understood. Furthermore, to investigate whether these adaptations are potentially transferred to an untrained limb (i.e., cross-education phenomenon) could be especially relevant during limb-immobilization frequently observed in older people (e.g., after hip fracture).

**Methods:**

At least 30 well-functioning older participants (>65 years) will participate in a within-person randomized controlled trial. After an 8-week control period, the effects of two 12-week PRT programs using light vs. heavy loads will be compared using an unilateral exercise model through three study arms (light-load PRT vs. non-exercise; heavy-load PRT vs. non-exercise; and light- vs. heavy- load PRT). Muscle-tendon function, muscle excitation and morphology and physical function will be evaluated to analyze the load-specific effects of PRT in older people. Additionally, the effects of PRT will be examined on a non-exercised contralateral limb.

**Discussion:**

Tailored exercise programs are largely demanded given their potentially greater efficiency preventing age-related negative consequences, especially during limb-immobilization. This trial will provide evidence supporting the use of light- or heavy-load PRT on older adults depending on individual needs, improving decision making and exercise program efficacy.

**Clinical Trial Registration:**

NCT03724461 registration data: October 30, 2018.

## Introduction

Resistance training has become a core component of exercise prescribed for older adults due to its capacity to mitigate the effects of aging on neuromuscular function and improve functional capacity (Liu and Latham, 2009; Peterson et al., 2010; Borde et al., 2015; Lopez et al., 2018). Recent recommendations for resistance training for older adults suggest to include power-oriented exercises (i.e., concentric movements performed as fast as possible) (Fragala et al., 2019). This is because muscle power is more closely related to physical function than muscle strength (Bean et al., 2003; Alcazar et al., 2020) and, therefore, considered the most robust biomarker of age-related neuromuscular decline. Moreover, power-oriented resistance training (PRT) has shown greater effects on physical function than traditional resistance training in older adults (Tschopp et al., 2011; Byrne et al., 2016; Ramirez-Campillo et al., 2016).

Despite its undisputed functional relevance, scant data are available to inform the proper prescription of PRT in older adults (Steib et al., 2010; Borde et al., 2015; Csapo and Alegre, 2016). The general goal of PRT is to execute concentric muscle actions with maximal velocity to maximize power output. However, a large variety of exercises (Franchi et al., 2019; Van Roie et al., 2020), resistance types (i.e., pneumatic, isotonic, body weight) (Sayers and Gibson, 2010; Van Roie et al., 2020), and intensities (i.e., loads used) (de Vos et al., 2005; Reid et al., 2015) can be found in the literature. In the last years, several previous studies have been performed with the intent to determine the optimal load for power development in older people (de Vos et al., 2005; Reid et al., 2015; Richardson et al., 2019). Summarizing these works in a systematic review, Katsoulis et al. (2019) concluded that a wide range of intensities may be used to improve muscle power and physical function in older adults. However, the variability of outcome measures and limited power of the studies included prevented the authors from performing a meta-analysis. For this reason, the authors recommended that further investigations comparing different intensities or frequencies of training and addressing force- or velocity-dependent components of the power adaptations should be conducted (Katsoulis et al., 2019). Therefore, well-designed studies using standardized testing procedures to compare the effects of PRT as performed using different loads in older adults are warranted.

To improve the quality of evidence, future studies should (i) compare volume × load-matched interventions (Csapo and Alegre, 2016); (ii) include a control period before interventions in order to account for the error of measurement, biological variability and training effect during testing (Hopkins, 2000); and (iii) use unilateral exercise model designs to allow for within-person comparisons to be made (Burd et al., 2010; Mitchell et al., 2012; Alegre et al., 2015; Pandis et al., 2017). This latter recommendation helps to increase statistical power by reducing between-person variability and limiting co-founding factors like nutrition, sleep, and physical activity (MacInnis et al., 2017). Additionally, unilateral exercise models provide the opportunity to investigate the cross-education phenomenon, which may help to estimate the neural and muscular contributions to PRT-related strength gains. Cross-education is mainly characterized by an increase in maximal voluntary force observed in the contralateral untrained limb (Munn et al., 2004; Lee and Carroll, 2007). Previous evidence was focused on the adaptations provoked by traditional heavy resistance training on maximal voluntary force (i.e., 1RM and maximal isometric force), whereas limited evidenced is available about cross-education phenomenon during isometric (Hester et al., 2019a) or dynamic (Hester et al., 2019b) ballistic actions following PRT in older people. Moreover, it could be expected that the load used during PRT influences the magnitude of the cross-education phenomenon (Cirer-Sastre et al., 2017; Colomer-Poveda et al., 2019, 2020). Hence, it deserves to be examined whether specific cross-education adaptations might be driven by different loads during PRT. This would enhance training prescription during limb immobilization and rehabilitation programs, especially in older people who are susceptible to long-term immobilizations after falling (e.g., hip fracture) associated to substantial neuromuscular declines and attenuated retraining capacity (Suetta et al., 2009).

Considering the above suggestions, this manuscript serves to present a protocol for a series of studies comparing the effects of heavy- vs. light-load PRT in older people. The main aim of this project is to assess the adaptations provoked by two volume × load-matched PRT programs using heavy vs. light loads in older adults (goal 1). The secondary aim is to investigate the adaptations provoked by heavy- vs. light-load PRT on the contralateral limb in older adults (goal 2).

## Methods/Design

### Experimental Approach

The present project and study protocol were registered in clinicaltrials.gov (ID: NCT03724461, October 30th, 2018) and approved by the Clinical Research Ethics Committee of the Complejo Hospitalario de Toledo (Spain). The study protocol will be conducted following the SPIRIT (Standard Protocol Items: Recommendations for Interventional Trials) statement (Chan et al., 2013). The intervention and data collection will be conducted at the University of Castilla-La Mancha, Toledo (Spain). This is a within-person randomized trial, including an 8-week control period followed by 12 weeks of PRT (Figure 1). The mean changes observed during the 8-week control period will be quantified to determine the possible extent of spontaneous changes in all outcome measures. After completing the control period, the participants will be randomized to one of the following study arms based on the treatment applied to their lower-limbs during the 12-week PRT program: (i) one leg will perform a light-load PRT and the other leg will not perform any exercise; (ii) one leg will perform a heavy-load PRT and the other leg will not perform any exercise; and (iii) one leg will perform a heavy-load PRT and the other leg will perform a light-load PRT. Assessments will be conducted at baseline (week 0), at the end of the control period (week 8), and following the 12-week PRT (week 20).

**FIGURE 1 F1:**
[figure not shown]
Flowchart of the study protocol.

### Participants

The sample size was determined by an *a priori* power analysis using G^∗^Power v3 software for MS Windows^®^ (Faul et al., 2007). The effect size value used for calculations was *d* = 0.25 based on a previous study comparing peak power adaptations after a 12-week heavy- vs. light-load PRT in older adults (de Vos et al., 2005). Then, we considered three levels for the between-subject factor (i.e., one for each study arm) and three levels for the within-subject factor (i.e., three repeated measures) setting the alpha error probability at 0.05, a 1−β of 0.95 and assuming a correlation among repeated measures of *r* = 0.8. The model indicated a minimum total sample size of 24 individuals, but considering a 25% dropout rate, we have decided to enroll at least 30 participants in total. People aged 65 years and over, non-institutionalized and without serious mobility limitations will be encouraged to participate. Principally, the volunteers will be recruited among participants involved in non-exercise studies previously conducted by our research group, local advertisements posted in public places and informative talks about healthy aging. After accepting to participate, the volunteers will undergo a physical examination by a geriatrician. The criteria for exclusion are: (i) frailty status (Fried et al., 2001) or low levels of physical function (i.e., Short Physical Performance Battery <7 points) (Guralnik et al., 1994), (ii) neurological, musculoskeletal, or other disorders that might preclude subjects from completing the resistance training and all performance tests, (iii) uncontrolled hypertension, unstable or exercise-induced angina pectoris or myocardial ischemia or any other medical condition that would interfere with testing or increase subjects’ risk of complications during exercise, (iv) history of regular resistance exercise during the previous 3 years, and (v) total or partial knee replacement (i.e., prosthesis). All participants will be informed orally and in written form about the purpose, procedures, benefits, risks, and potential discomfort related to study participation before signing a consent form. This study will be conducted in accordance with the Helsinki declaration.

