### Statistical Analysis

Data will preferentially be presented as mean ± standard deviation. Normality of distribution will be assessed by the Shapiro–Wilk test and log-transformed in case of non-normal distribution. As preference, the outcomes will be registered as the absolute (Post – Pre) and relative [(Post – Pre)/Pre] change during the 8-week control period and the 12-week PRT program. Given the hierarchical structure and correlated data contained in our investigation (each participant will contribute to observations in two different groups), the existence of partially paired data must be considered for comparison purposes. Thus, linear mixed effect models will be used to assess the goals proposed for the present investigation. To assess the adaptations provoked by two volume × load-matched PRT programs using heavy vs. light loads in older adults (goal 1), changes noted in the legs undergoing HL-PRT and LL-PRT (i.e., week 20-week 8) and those noted in the same legs during the control period (i.e., week 8-week 0) will be compared with treatment (HL-PRT vs. LL-PRT vs. control) as a fixed factor, participants as a random factor and baseline values as a covariate. To investigate the adaptations provoked by heavy- vs. light-load PRT on the contralateral limb in older adults (goal 2), changes noted in the contralateral non-exercising legs of those legs performing either HL- or LL-PRT (i.e., week 20-week 8) and those noted in the same legs during the control period (i.e., week 8-week 0) will be compared with treatment (HL-PRT vs. LL-PRT vs. control) as a fixed factor, participants as a random factor and baseline values as a covariate. The models will be calculated considering maximum likelihood estimation and the best-fitting covariance structure. Bonferroni corrections will be applied for the *post hoc* pairwise comparisons and the Cohen’s *d* effect sizes will be calculated and classified as trivial (0.20), small (0.20–0.49), moderate (0.50–0.79), and large (>0.8) (Cohen, 1988). Potential adverse events and drop-outs will be compared between groups by Chi-squared tests. All statistical analyses will be performed using IBM SPSS Statistics for Windows Version 24.0 (IBM Corp. Armonk, NY, United States), and the level of significance will be set at α = 0.05.

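### The stated N of 24 follows only if 0.25 is Cohen's f, not the printed d, and the test it powers is not in the planned models, so 95% power is not shown for the heavy- versus light-load contrast.

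*Protocol article*

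**What the plan says.** The Participants section gives the effect size and its origin: "The effect size value used for calculations was *d* = 0.25 based on a previous study comparing peak power adaptations", the comparison being heavy- against light-load training over 12 weeks. The design entered in G*Power had "three levels for the between-subject factor (i.e., one for each study arm) and three levels for the within-subject factor", "setting the alpha error probability at 0.05, a 1−β of 0.95", and the calculation proceeded "assuming a correlation among repeated measures of *r* = 0.8". It returned 24 people in total. Allowing for 25% dropout, the plan enrols at least 30, allocated equally to the three arms.

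The Statistical Analysis section uses the same symbol for Cohen's d: "the Cohen’s *d* effect sizes will be calculated and classified as trivial (0.20), small (0.20–0.49), moderate (0.50–0.79), and large (>0.8"). For each of the two goals it fits a linear mixed model to leg-level changes (week 8 to 20, and week 0 to 8), which "will be compared with treatment (HL-PRT vs. LL-PRT vs. control) as a fixed factor", with participant as a random factor and baseline as a covariate. Post hoc pairwise comparisons are Bonferroni-corrected.

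**The concern.** There are two separate problems. First, d and f are different scales. For two groups f = d/2, so the same 0.25 describes an effect twice as large when read as f as when read as d. On the article's own classification, d = 0.25 is small, whereas f = 0.25 corresponds to a moderate d. A reader who takes the printed symbol at face value will believe that 24 people give 95% power for a small difference between loads.

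Second, the calculation treats study arm as the between-subject factor and time as the within-subject factor. The analysis compares treatments given to legs, and in the third arm one participant supplies a leg to each treatment. The power of one test does not carry over to the other. Heavy versus light load is the main aim of the project, so readers will weigh a non-significant result on that contrast by the power the article claims.

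**Working it through.** **Inputs from the article:** effect 0.25; k = 3 arms; m = 3 measurements; alpha = 0.05; power 0.95; rho = 0.8; N = 24; enrolment 30; dropout 25%. The article does not name the F test.

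**Reproducing 24.** For the within-between interaction (sphericity assumed), lambda = f²·N·m/(1 − rho), df1 = (k − 1)(m − 1) = 4, df2 = (N − k)(m − 1) = 2(N − 3). With f = 0.25:

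- N = 21: lambda = 0.0625 × 21 × 3/0.2 = 19.69, df2 = 36, power 0.933.
- N = 23: lambda = 21.56, df2 = 40, power 0.956.
- N = 24: lambda = 22.50, df2 = 42, power 0.965.

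So 24 is the first total in equal thirds that reaches 0.95. Other tests with f = 0.25 and the same inputs do not give it: within-subject main effect 21, between-subject main effect 219, and the interaction under the two alternative effect-size conventions in G*Power 156 and 153.

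**Reading 0.25 as d.** f = 0.25/2 = 0.125:

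- N = 24: lambda = 0.015625 × 24 × 3/0.2 = 5.63, power 0.399.
- N = 30: lambda = 7.03, power 0.502.
- N = 82: power 0.951; in equal thirds, N = 84: 0.956.

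Main-effect tests at f = 0.125 need 69 (within) or 861 (between). Spreading d = 0.25 over three means in other ways gives f of 0.102 to 0.118 and N of 93 to 123. No reading as d gives 24.

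**Converting the other way.** f = 0.25 is d = 2 × 0.25 = 0.5 for two groups. For the extremes of three equally spaced means, f = d·√(1/6), so d = 0.25/0.408 = 0.61.

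**Powered test against planned test.** The powered term is arm by time on three measurements. The planned models have one three-level treatment factor on leg changes, and no arm, time or arm-by-time term. Randomisation follows week 8, so allocation cannot produce an arm difference in the first interval.

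**Heavy versus light load as planned.** Per arm of n completers there are n within-person pairs (third arm), n heavy-only legs and n light-only legs. Assumptions not in the article: d is in SDs of the outcome at one time point; residual SD after baseline adjustment is √(1 − 0.8²) = 0.6; between-leg correlation r is 0 to 0.7. Then:

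- paired variance = 2 × 0.36 × (1 − r)/n; unpaired variance = 2 × 0.36/n;
- the two are combined by inverse variance, with a noncentral t on 3n − 4 df;
- the Bonferroni level for three contrasts is 0.05/3 = 0.0167.

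For example, at n = 10 and r = 0.7 the variances are 0.0216 and 0.072, the combined variance is 0.0166 and the SE is 0.129.

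| n per arm | r | SE | d = 0.25: 0.05 / 0.0167 | d = 0.5: 0.05 / 0.0167 | Detectable, 80% power, alpha 0.05 |
|---|---|---|---|---|---|
| 8 | 0 | 0.212 | 0.201 / 0.097 | 0.611 / 0.419 | 0.63 SD |
| 8 | 0.3 | 0.193 | 0.235 / 0.118 | 0.695 / 0.507 | 0.57 SD |
| 8 | 0.7 | 0.144 | 0.379 / 0.217 | 0.910 / 0.795 | 0.42 SD |
| 10 | 0 | 0.190 | 0.245 / 0.126 | 0.718 / 0.538 | 0.55 SD |
| 10 | 0.3 | 0.172 | 0.287 / 0.154 | 0.798 / 0.636 | 0.50 SD |
| 10 | 0.7 | 0.129 | 0.463 / 0.288 | 0.962 / 0.897 | 0.38 SD |

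Eight per arm is the plan's 24; ten per arm is 30 with no loss. A 25% loss from 30 leaves 22.5, slightly below eight per arm.

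**Goal 2.** Only two arms have an untrained leg, so the load comparison is n versus n with SE = √(0.72/n). The detectable difference at 80% power and alpha 0.05 is 0.91 SD with 8 per arm and 0.80 SD with 10.

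**The case against.** The best defence is that one symbol is wrong and the calculation is right: 0.25 was an f, was entered as an f, and was printed as d. The article cannot exclude this. It attributes the value to an earlier study that is not reproduced, and under this reading the stated test has 96.5% power. A reader might therefore go too far in several directions.

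- That a heavy-versus-light d was fed in on the wrong scale. The two-group origin of the value and the later use of d make this plausible, but nothing in the article decides it.
- That the 95% power is definitely not achieved. At d = 0.5 with 10 per arm and r = 0.7, the planned contrast reaches 0.96 without Bonferroni. The supportable statement is that 95% is not shown.
- That power is lower for every reported contrast. Power for either load against control depends on a training effect the article does not give. Even for heavy versus light load, a high between-leg correlation brings power close to the interaction's 0.50 at N = 30.
- That a null result will be read as equivalence. No equivalence test or margin is planned, so this would be an interpretive risk, not a planned inference.
- That goal 2 is a sample-size failure. The article already calls it secondary, and a sample size need not power a secondary aim.

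What the defence leaves standing is that the printed metric does not yield the printed N, and that the powered interaction is absent from both planned models.

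**Conclusion.** The point holds in this form. As written, the effect metric and the sample size are inconsistent: 24 needs f = 0.25, and the printed d = 0.25 gives the same test about 0.40 power at 24 and 0.50 at 30. Which of the two was intended is unknown. Under both readings the stated 95% belongs to a test the analysis does not perform.

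For the planned heavy versus light load contrast, power is about 0.20 to 0.46 if d = 0.25 (0.10 to 0.29 with Bonferroni) and about 0.61 to 0.96 if d = 0.5 (0.42 to 0.90 with Bonferroni). These ranges rest on the assumed residual SD of 0.6, a between-leg correlation of 0 to 0.7, and 8 to 10 completers per arm. The mismatch itself needs none of those assumptions.

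**What to change.** Correct the sample-size paragraph in the Participants section and leave enrolment as it is.

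1. State the metric. Either declare f = 0.25, equivalent to d of about 0.5 to 0.6, and justify an effect of that size; or keep d = 0.25 and restate power for the interaction as about 0.40 to 0.50.
2. In either case, report power or the detectable difference for the planned heavy versus light load contrast after expected dropout, with the between-leg correlation given as an assumption. At 80% power and alpha 0.05, for correlations from 0.7 to 0.3, the detectable difference is about 0.42 to 0.57 SD with 8 per arm or 0.38 to 0.50 SD with 10.
3. Goal 2 is already secondary and needs no relabelling. If a detectable difference is quoted for it, it is about 0.8 to 0.9 SD.

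The cost is a reworded paragraph and, probably, a less favourable power statement. No participants are added and the analysis does not change.

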### Randomization and Allocation of Participants

After completing the control period, the participants will be stratified by their sex and 1RM values and randomly allocated in equal numbers to the three intervention groups. Then, the treatment applied to the subjects’ legs will be determined by coin toss.

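### The floor of 30 participants covers 20% dropout, not the stated 25%: 24/0.75 is 32, whereas 30 is 24 × 1.25; the effect on power is very small

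*Protocol article*

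**What the plan says.** The sample size is set in the protocol article, Methods/Design, Participants. The power analysis is followed at once by the dropout allowance: "minimum total sample size of 24 individuals, but considering a 25% dropout rate, we have decided to enroll at least 30 participants in total". The target power is given as "a 1−β of 0.95". The abstract repeats the floor of 30 and gives no higher target. No other section offers a second dropout allowance or a different rule for inflating the sample.

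Two further statements bear on the point. Under Randomization and Allocation of Participants, those who finish the control period are "randomly allocated in equal numbers to the three intervention groups". Under Experimental Approach, randomisation comes only after that 8-week control period, so some losses may occur before anyone is allocated.

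**The concern.** The sentence presents 30 as the number that protects a minimum of 24 against 25% loss, and it does not do so. The usual slip is to multiply the required number by one plus the dropout rate instead of dividing by one minus it, and the stated figure is exactly what that slip gives.

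At stake is the consistency of the trial's only sample-size justification. If enrolment stops at the floor and dropout is as the plan expects, the trial ends with fewer participants than the plan calls its minimum. The question is then whether the lost power matters.

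**Working it through.** **Inputs, all from the Participants section.** Effect size: "The effect size value used for calculations was *d* = 0.25". Alpha: "setting the alpha error probability at 0.05". Power target 0.95. Three study arms (k = 3) and three repeated measures (m = 3). Correlation: "assuming a correlation among repeated measures of *r* = 0.8". Minimum 24, dropout 25%, enrolment at least 30.

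**Step 1: reproduce the 24.** The model is a repeated-measures ANOVA, within-between interaction, with power from the noncentral F distribution. Sphericity is assumed, and 0.25 is taken as Cohen's f, the reading that gives the plan's figure.

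- Noncentrality: λ = f² × N × m / (1 − r) = 0.0625 × N × 3 / 0.2 = 0.9375 × N
- Degrees of freedom: (k − 1)(m − 1) = 4 and (N − k)(m − 1) = 2(N − 3)

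The smallest N with power of at least 0.95 is 23, or 24 if the arms are to be equal. The plan's 24 therefore reproduces.

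**Step 2: the dropout allowance.**

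- Enrolment that leaves 24 after 25% loss: 24 / (1 − 0.25) = 32
- What the plan's figure corresponds to: 24 × 1.25 = 30
- Completers from 30 at 25% loss: 30 × 0.75 = 22.5, so 22 to 23
- Loss that 30 can absorb: 1 − 24/30 = 0.20

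The floor is 2 participants short of the matching enrolment.

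**Step 3: what the shortfall costs in power.** The model is that of Step 1.

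| Completers | λ | Second df | Power |
|---|---|---|---|
| 24 | 22.50 | 42 | 0.965 |
| 23 | 21.56 | 40 | 0.956 |
| 22 | 20.63 | 38 | 0.946 |

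The expected number of completers straddles the 0.95 target: 23 meets it, and 22 misses it by about 0.004. Measured against the power target instead of the stated 24, the floor is one participant short, since 23/0.75 = 30.7, which rounds up to 31.

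**The case against.** The strongest reply is that nothing of substance changes.

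- **The target is 0.95, and 23 completers meet it.** The figure of 24 includes some slack from rounding to equal arms. This stands, and it is why the point is minor.
- **The 30 is a floor.** The plan lets the investigators enrol 32 or more without an amendment. This stands as far as it goes: the minimum is missed only if enrolment stops at or near 30. It does not rescue the sentence, which offers the floor itself as the allowance for 25% dropout.
- **The power figures count completers only.** The Statistical Analysis section plans linear mixed models on change scores and includes the control-period changes. A participant lost after week 8 can still contribute one of those. This also stands. Differences of about 0.005 in power are finer than the ANOVA calculation can support.
- **The 25% might mean six extra participants on top of 24.** The text calls it a dropout rate, and six lost out of 30 is 20%. On that reading the label is wrong instead of the number, and the sentence still needs correcting.

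A reader might also infer more than the documents support, in three ways.

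- *That 33 participants are required.* That figure comes from 8/0.75 = 10.67, hence 11 per arm. It holds only if all losses follow randomisation and 8 completers per arm are wanted. Because allocation follows the control period, some losses can precede it, and 32 enrolled can suffice.
- *That power falls to 0.933.* That is the value at 21 completers, 7 per arm. Losing 9 of 30 is a 30% loss, not 25%, and the plan nowhere requires equal numbers of completers.
- *That the loss should be measured from 0.965.* That is the power at 24, which overshoots the target. The plan's own criterion is 0.95.

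**Conclusion.** The sentence is wrong as written. The stated minimum, dropout rate and enrolment floor cannot all hold together, and no other part of the document reconciles them. The error is 2 participants in the enrolment figure, or equivalently 5 percentage points in the dropout that the figure covers.

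The documents do not support calling the trial underpowered on this account: at the expected number of completers, power stays at about the planned level.

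The dropout arithmetic needs no assumption beyond the ordinary meaning of a dropout rate. The power values assume sphericity, an analysis of completers only, enrolment of exactly 30, and 0.25 as Cohen's f. The protocol labels that effect size d. Whether the label or the value is right is a separate question and does not affect the dropout arithmetic.

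**What to change.** Correct the sentence in Participants in one of two ways.

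1. Keep 30 and change the rate: state that 30 enrolled allows for 20% dropout (30 × 0.80 = 24).
2. Keep 30 and 25%: state that 22 to 23 completers are expected, with power of about 0.95 (0.946 to 0.956).

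Either costs one sentence and no extra recruitment. The only loss is a slightly less favourable statement of the dropout allowance or of the completers expected. If the sponsor prefers to keep both 25% and a minimum of 24, the matching enrolment is 32, two more than the present floor, and the abstract should carry the same figure.
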